**Limitations**

1) Generalizability. As with all population-based studies, our results may not be generalizable to other groups of women. We anticipate that our findings will be generalizable to other groups of similarly-aged women in settings with similar prevalence rates of HPV and adherence to diaphragm use.

2) Co-interventions. Although randomization will allow for equal distribution of both known and unknown confounders, the nature of the trial and intervention may allow for co-interventions that account for differences that may be observed between the two groups. For example, women who use the diaphragm may be more apt to douche which may in turn affect prevalence rates of HPV. We will collect information on plausible interventions and control for these in the analyses. In addition, the lubricant gel may interfere with the PCR-based test for HPV. We are performing a pilot study to determine any interference. If interference is demonstrable, we will stratify analyses by time from last diaphragm use. We do not believe that the gel will affect cytologic or histologic outcomes nor will it affect enrollment HPV results obtained before the subject uses the diaphragm.

3) Power. Although we believe that we will have adequate power to test our main study hypotheses, we may have limited power to perform subgroup analyses that may be important.

4) Subject adherence to follow-up and protocol. We have devised plans to assure subject retention. We will stress the importance of adherence to study protocol and will assure that women have all the information to make informed choices about participation in all aspects of the study,

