## Product Administration Plan

At enrollment, women randomized to the diaphragm group are fitted for diaphragm size and receive an Ortho All-Flexdiaphragm. Staff also instruct women about how to use the Replens gel and how to properly clean and store their diaphragms and gel applicators***.***

To improve diaphragm compliance during the trial, only women who are able to correctly insert the diaphragm are enrolled into the study. In order to avoid introducing a bias between the study arms, all women practice diaphragm insertion *before* they are randomized. Women who are not able to correctly insert/remove the diaphragm after five attempts are not eligible to enroll into the study. Following randomization, women in the diaphragm arm will receive condoms, a diaphragm and gel, and more counseling. Women in the condoms-only arm receive condoms and counseling and are told that they can receive a diaphragm to keep and use as they wish at the end of their participation in the study.

Throughout the study, we encourage women to return to the study site if they experience any problems using the diaphragm or would like further instructions or advice. We also ask women to return to the clinic or mobile site at any time during the study if they feel discomfort. A clinician provides a larger- or smaller-sized device as needed. Women who have a vaginal delivery during the study are re-fitted for diaphragm size. As part of ongoing quality assurance processes, there are systematic checks of diaphragm fittings, which sometimes result in a woman being fitted with a new diaphragm size. Replacements for damaged or lost diaphragms can be obtained in the clinic at any time during the study or can be distributed through home visits when compatible with confidentiality requirements.

Women are instructed to insert the diaphragm at any time before sex. We ask them to put lubricant gel in the dome and rim of the diaphragm at the time of insertion and to reapply gel in the vagina before each act of vaginal sex. We ask them not to cleanse the vagina or the diaphragm immediately after sex but to leave the device in place for at least 6 hours. Staff also instruct women about how to properly clean and store their diaphragm and gel applicator. Women are allowed to resume normal vaginal hygiene after sexual intercourse (*i.e.* cleanse outer genitalia with water or water and soap) as long as they do not remove the diaphragm within six hours after sex.

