**Study Hypotheses and Specific Aims**

***1. Diaphragm use will decrease the incidence of HPV.*** We propose to collect samples at each visit for HPV testing and typing by PCR in the randomized cohort of Zimbabwean women. We will determine the effect of diaphragm use on the rates of incident infections.

***2. Diaphragm use will decrease the persistence of HPV.*** We will determine the effect of diaphragm use on persistence of HPV in women found to be positive at enrollment.

***3. Diaphragm use will decrease the incidence of cervical cytologic abnormalities.*** Women will receive cytologic evaluation at enrollment and exit. We will determine the effect of diaphragm use on the rates of cytologic abnormalities.

***4. HPV infection increases the risk of male-to-female vaginal HIV transmission.*** We hypothesize that HPV infection will result in recruitment of a local immune response, which might place women at increased risk for heterosexual HIV acquisition. We will compare the rates of HIV acquisition in HPV-negative *versus* HPV-positive women. In addition, we will examine the effect of HPV viral load on HIV transmission.

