**Methods**

This study will be offered to women enrolled in the Zimbabwe cohort of the diaphragm effectiveness trial (MIRA). Separate consent will be required to participate in this sub-study. Enrollees will be informed of the following additional testing to be performed (See Chart A: HPV study flow sheet). Neither study participants nor providers will be informed of HPV results nor will the results be used to direct clinical management.

• Enrollment visit: cytology and cervical swab for HPV testing

• 3 month visit: self-swab for HPV testing

• 6 month visit: self-swab for HPV testing

• 9 month visit: self-swab for HPV testing

• 12 month visit: self-swab and cervical swab for HPV testing

• 15 month visit: self-swab for HPV testing

• 18 month visit: self-swab for HPV testing

• 21 month visit: self-swab for HPV testing

• 24 month visit or last visit: cytology and cervical swab for HPV testing

**Cytologic sample collection and analysis:** At the time of the enrollment visit pelvic examination, a sample for cytology will be obtained from the endo- and ecto-cervix with a spatula and an endocervical brush. The specimen will be smeared onto a glass slide and then fixed immediately using hairspray (or another fixative). Cytology will be stained and interpreted in Zimbabwe where reliable cytology services have been available for the past 10 years (personal communication, [name]). Cytopathologists will be blinded to the arm of the study to which participants have been randomized.

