**HPV sample collection:** At the enrollment visit, after the cytology sample is taken, the cervix and endocervix will be swabbed under direct visualization with a Dacron swab and stored in Sample Transport Medium (Digene Diagnostics, [name]) at 40C.. At follow-up visits, participants will be instructed in the technique of self-sampling and these samples will be stored in specimen transport medium as stated above. At the 12 month follow-up visit, a clinician-collected swab will be collected in addition to the self-collected swab. At study exit, a final clinician-collected swab will be obtained under direct visualization at the time of pelvic examination. Study exit will vary from 12 to 24 months depending on time of enrollment. Samples will be shipped to UCSF with cold packs for analysis in the laboratory of [name] by PCR using MY09/11 primers (see below). In addition, quantification of HPV levels will be performed by real-time PCR in HPV-positive samples from all women who sero-convert to HIV and a matched sample of controls who do not sero-convert. These will be reported as viral loads. Currently [name] laboratory has PCR primers and probes for quantitative PCR in HPV 16, 18 and 33-positive samples, and is developing assays for the remaining high risk HPV types.

**Secondary study outcome: Cervical dysplasia, biopsy-confirmed.** Women with abnormal Pap tests interpreted as AGUS, HSIL, adenocarcinoma in situ and cancer will be referred for immediate colposcopy. Women with Pap results of ASCUS or LSIL will undergo a repeat Pap smear after 6 months. If the results indicate ASCUS or worse, she will be referred for colposcopy. At the time of the exit Pap test, the threshold for referral will remain the same as at previous visits (cytologic abnormalities of AGUS, HSIL or worse). Women with exit Pap results of ASCUS or LSIL will be counseled and referred to local clinics for repeat Pap smears 6 months later. Colposcopists will be blinded to the arm of the study to which participants have been randomized. Women with colposcopic abnormalities will undergo diagnostic biopsies, and those with cervical intraepithelial neoplasia (CIN) 2 or 3 will undergo loop electrosurgical excision procedure. Women found to have cancer will be referred for cancer treatment. Histological analyses of biopsy and loop specimens will be performed in Zimbabwe. All colposcopic and histological data will be entered on a case report form and transferred to UCSF.

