**Testing quality control.** [name] laboratory performs extensive quality assurance and quality control measures with each HPV assay. Because of its high sensitivity, PCR by definition must be performed with great care to avoid the possibility of contamination. The laboratory takes all possible precautions in handling samples, including separation of pre- and post-amplification products in different parts of the research building. Each run contains several random negative control specimens and positive controls for each HPV type being sought. His laboratory will also use HPV-positive tissue culture cells containing known numbers of HPV 16 copies as a sensitivity control. If any of the above negative and positive controls do not work, the reaction is repeated. The lab performs a large volume of HPV testing for several studies and to date has not had problems with contamination. Each specimen is also studied for the presence of beta-globin as a positive control for human DNA and for the overall amplification procedure. If a specimen is negative for beta-globin it is presumed that an inadequate specimen was obtained, that the reaction failed or that the specimen contained an inhibitor of the PCR reaction. In their experience this occurs in less than 5% of the specimens, and the HPV results from the specimen are excluded from analysis. As a final quality control measure, [name] laboratory participates in routine exchange of cervical specimens with the other laboratory performing PCR in the WIHS, the laboratory of [name]. The results of PCR detection are compared between the two labs, including the detection of specific types. In the past they have had excellent agreement and continue to do so.

For cytology quality control, a random sampling of 10% of normal and 100% of abnormal cytologic samples will be shipped to UCSF and reviewed by co-investigator [name] of the Department of Pathology at UCSF. Due to regulatory constraints in Zimbabwe, histologic specimens cannot be released for outside review.

**Definitions of abnormal tests.**  All cytologic specimens will be interpreted using the 1991 Bethesda System 63. As per standard practice, we will consider a Pap smear “abnormal” if interpreted as atypical squamous cells (ASCUS), low-grade squamous intraepithelial lesion (LSIL), atypical glandular cells (AGUS), high-grade squamous intraepithelial lesion (HSIL) or squamous cell carcinoma.

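### HPV sub-study: stratifying by time since last diaphragm use cannot correct gel interference with the PCR, because control women have no such time

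*Protocol*

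**What the plan says.** Appendix 16.2 tests two PCR-based hypotheses between the randomised arms. For incidence, the aims section says: "We will determine the effect of diaphragm use on the rates of incident infections". For persistence, the statistical methods compare clearance between arms among women positive at baseline. Follow-up specimens are mostly self-collected at quarterly visits (for example "3 month visit: self-swab for HPV testing"), with clinician swabs at month 12 and at exit.

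Under Limitations the appendix concedes that "the lubricant gel may interfere with the PCR-based test for HPV" and mentions a pilot study. The response to a positive pilot is: "If interference is demonstrable, we will stratify analyses by time from last diaphragm use". The same paragraph expects no effect of the gel on cytology, histology or the enrolment HPV results.

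There is one other safeguard. Under testing quality control, "If a specimen is negative for beta-globin it is presumed that an inadequate specimen was obtained", or that the reaction failed or was inhibited, and that specimen's HPV result is dropped.

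On exposure, the Product Administration Plan in the main protocol gives diaphragm and gel to one arm. Control women are "told that they can receive a diaphragm to keep and use as they wish at the end of their participation in the study". Women in the diaphragm arm put gel in the device at insertion and "reapply gel in the vagina before each act of vaginal sex".

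**The concern.** Only the diaphragm arm uses the gel, so any loss of PCR sensitivity that it causes falls on that arm alone. A missed positive lowers apparent incidence. In a woman who was positive at baseline it also looks like clearance. Both errors point towards protection, which is the direction of hypotheses 1 and 2 and of the one-sided tests on which the power section relies.

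The remedy has to separate an assay artefact from a real effect. If it cannot be applied to the control arm, it leaves the between-arm comparison as it was, and the sub-study could credit the diaphragm with part of an effect that arises in the laboratory.

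**Working it through.** **Can the strata be formed in both arms?**

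- *Diaphragm arm:* time since last use exists at each follow-up visit for any woman who has used the device.
- *Control arm:* the only insertion is the supervised practice before randomisation. No meaningful value exists at any follow-up visit.
- *Result:* each stratum contains diaphragm-arm women only, so there is no within-stratum randomised contrast. Setting one stratum against all controls is possible, but the stratum is chosen by behaviour after randomisation. Women long past last use are likely to be less adherent or to have had less recent sex, and recent sex bears on HPV exposure.
- *Wrong clock:* the suspected agent is the gel, which is reapplied before each act, so diaphragm timing is only a proxy for gel exposure.

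**How large could the bias be?** The protocol gives neither the size of the interference nor the share of swabs exposed, so there is no stated figure to reproduce. What follows is a set of scenarios.

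Inputs from the power section of the appendix: high-risk HPV incidence 8% per year and clearance 65% per year in controls, both read as annual probabilities. From the visit schedule: 8 quarterly swabs over 24 months. Assumed: no true effect, an average sensitivity loss *l* in the diaphragm arm of 16%, 26% or 37%, independent misses, the first negative counted as clearance, and no beta-globin exclusion.

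*Clearance.* The quarterly probability of staying positive is 0.35^(1/4) = 0.769, so true clearance per visit is 1 − 0.769 = 0.231. With misses, apparent clearance per visit is 1 − 0.769 × (1 − *l*):

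| *l* | apparent clearance per visit | ratio to 0.231 |
|---|---|---|
| 16% | 1 − 0.769 × 0.84 = 0.354 | 1.53 |
| 26% | 1 − 0.769 × 0.74 = 0.431 | 1.87 |
| 37% | 1 − 0.769 × 0.63 = 0.516 | 2.23 |

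*Incidence.* An infection missed once can be found at a later visit. With long follow-up the share of infections ever detected is (1 − *l*) / (1 − 0.769 *l*), which is 0.96, 0.93 and 0.88 for the three losses. Finite follow-up and late detection lower this. Simulation of the 8-visit schedule gives apparent incidence ratios of about 0.93–0.94, 0.88–0.89 and 0.83.

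*Sensitivity to reading 8% and 65% as rates.* The quarterly probability of staying positive becomes exp(−0.65/4) = 0.850. The clearance ratios are then (1 − 0.850 × 0.84)/0.150 = 1.91 at 16% and (1 − 0.850 × 0.63)/0.150 = 3.10 at 37%. The simulated incidence ratios are about 0.94 and 0.86.

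*Benchmarks.* Table 1 of the appendix gives least detectable relative hazards of 0.63 and 0.74 for incidence and 0.77 and 0.84 for persistence. The incidence bias does not reach its benchmarks at these losses. The clearance bias, inverted, is 1/1.53 = 0.65 to 1/2.23 = 0.45, beyond both persistence benchmarks (taking the table's hazard as oriented so that less persistence is below 1).

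*Effect of the beta-globin exclusion.* Take half of swabs exposed and half of exposed positives missed (*l* = 0.5 × 0.5 = 25%). The simulated clearance ratio is 1.84 with no exclusion, 1.42 if half of the interfered specimens are caught, 1.08 if 90% are, and 1.00 if all are. The incidence ratio stays near 0.9 throughout, because only the diaphragm arm loses visits at which an infection could be seen.

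**The case against.** **The beta-globin check already handles inhibition.** In part this stands. General PCR inhibition becomes missing data rather than a false negative, and if nearly all affected specimens are caught the clearance bias almost disappears. It does not catch partial or HPV-specific loss of sensitivity, and exclusions may be more frequent in the diaphragm arm.

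**The stratified look is still informative.** Apparent protection confined to women with recent use would point to interference, and the sentence does not say that it replaces the randomised analysis. As an artefact check within one arm this is fair. It is not a correction of the between-arm result, and the plan names nothing else for the case in which interference is shown.

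**An unseen analysis plan may settle the details.** It may, but the protocol itself fixes this remedy, and the remedy cannot work in the control arm.

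**Stronger readings that the documents do not support.** A reader might infer that a 16–37% sensitivity loss lowers apparent incidence by the same 16–37% and so mimics every powered effect. That holds for a single test, not for quarterly retesting, and 0.77 and 0.84 in Table 1 are persistence rows. A reader might also infer that the clinician swabs offer a clean comparison. Section 4 of the protocol says that the gel is meant to coat the cervix as well as the vagina, and the Limitations paragraph exempts only the enrolment HPV results. With swabs at months 12 and 24 only and equal interference, the simulated incidence ratio is about 0.86–0.67, which is worse than with quarterly swabs.

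**Conclusion.** The concern holds in a limited form. The stated stratification cannot be applied to controls, conditions on behaviour after randomisation and follows the wrong exposure, so it does not correct the incidence or persistence comparison.

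Clearance is the more exposed endpoint (ratio about 1.5–2.2 before any exclusion) and incidence the less exposed (about 0.93–0.83). These sizes rest on assumed losses, no true effect, independent misses, the appendix's control rates read as annual probabilities, and no beta-globin exclusion.

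It would go too far to infer that the sub-study will report false protection. That requires the pilot to find interference, the interference to take the form of false negatives, and the beta-globin check to miss a material share of it. Cytology, histology and the trial's HIV endpoint are outside this point. The sentence should be changed; the design of the trial is not in question.

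**What to change.** Replace the sentence in the Limitations of Appendix 16.2 with rules that apply to both arms:

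1. Keep beta-globin-negative specimens as missing, and report their frequency by arm and visit.
2. If the pilot shows interference, keep the randomised comparison and re-estimate the aim 1 and aim 2 effects in a bias analysis that uses the sensitivity loss measured in the pilot. Claim protection on the PCR endpoints only if it survives that analysis.
3. Show time since last gel or diaphragm use only as a descriptive artefact check within the diaphragm arm.

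Do not move the main comparison to clinician swabs unless the pilot shows that they are free of interference. If they are ever used this way, first reconcile their timing: the Methods place the middle clinician swab at month 12, while Chart A places it at visit 6, which is month 15 when enrolment is visit 1.

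The cost is a few lines of appendix text and a modest additional analysis of specimens already planned. The HPV result may turn out less favourable.

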**Protection of Human Subjects**

**Risks.** Participation in research may result in a loss of privacy, although safeguards to be described below will make this risk minimal. In general, the risks of this study are small. The major downside of this study is the time requirements imposed for completing all of the study visits. Colposcopy is a safe procedure, however, as with all procedures, there are risks. The risks include discomfort, pain, bleeding and infection. The procedure is well-tolerated by most women with pain associated with biopsy often described as mild to moderate and of short duration. Bleeding from biopsy sites is easily controlled by safe chemical cautery agents. Infection from this procedure is very rare.

**Disclosure of HPV results.** Results of HPV testing will not be disclosed to participants since the tests that will be used are not approved for clinical use by the Clinical Laboratory Improvement Act regulations. HPV infections are very common in this and other populations. There are no known treatments for HPV infection.

**Minimizing risks.** All materials with patient identifiers will be stored in a secure area. Study samples will be labeled only with a study code. Linkage between study codes and patient identifiers will be kept confidential. Therefore no patient identifiers will be attached to samples provided to this project. All colposcopies will be performed by trained professionals.

**Benefits.** Subjects returning to the clinic specifically for procedures related to this sub-study will receive a monetary reimbursement from participation. Otherwise, they will receive the standard reimbursement for their participation in the main study for each scheduled visit. Some women with cervical dysplasia and treatment, however, will benefit by having cancer averted. The improved understanding of the effect of diaphragm provision on HPV and cervical neoplasia outcomes may potentially be of benefit to large populations of similar women and may improve patient management.

**Consent Process and Documentation.** Participants will be required to give additional informed consent for procedures related to the sub-study. The option to participate is explained during the enrollment main study informed consent process. The decision to participate in the sub-study will in no way affect their ability to participate in the main study. All information in the informed consent forms will be translated into Shona and back-translated into English to ensure accuracy and clarity of the information being presented to eligible participants.

**Treatment and Compensation for Injury.** We are aware of the University of California policy on subjects’ treatment and compensation for injury as a result of participation in the proposed study. We have incorporated the UCSF required wording into the consent document. We anticipate no injuries will occur by subject participation.

**Alternatives.** Available treatment options will be unaffected by the subjects’ decision concerning participation in the proposed study.

**Confidentiality of Records.** We will take extensive precautions to maintain patient confidentiality throughout the study. No names or other identifying information will appear on any documents. While the study is on-going, we will keep patients’ names confidential through the use of patient ID numbers. We need to keep these identifiers to link measures at enrollment to measures at the study conclusion. We will maintain this information in locked files; after the study is complete we will destroy records linking patients’ names to study ID numbers. Patient identities will not be revealed in any publication that may result from the proposed study.

